### Patient population

2.3.

Patient enrollment for this ongoing study began in September 2022 at six medical partner institutions in Tokyo, Japan. The inclusion criteria were as follows: (1) patients diagnosed with non-cardiogenic stroke, (2) patients aged >20 years, and (3) patients or their families who agreed to participate in the study and provided informed consent. Patients with insertable cardiac monitor (ICM) were also participated if they met the inclusion criteria. The exclusion criteria were as follows: (1) patients who are currently participating or will participate in another intervention trial, (2) patients with AF or atrial flutter, (3) patients diagnosed with less than 1 year to live, and (4) patients judged by their doctor to be ineligible to participate in the study. A full description of the inclusion and exclusion criteria is presented in Table 1. Trained stroke rehabilitation nurses and physicians educated the registered patients on pulse palpation according to a standardized protocol that focuses on evaluating the heart rate and rhythm regularity. First, rehabilitation therapists were educated about the health implications of AF (i.e., the risk of ischemic stroke, thromboembolism, heart failure, and mortality), clinical presentation, and its frequent asymptomatic nature. The potential health benefits of the intervention were also explained.

**Table 1 tab1:** Inclusion and exclusion criteria.

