### Evaluations and follow-up

2.4.

The following parameters were evaluated: (1) feasibility of pulse checks in rehabilitation hospitals, (2) proportion of AF detection, and (3) proportion of initiation of anticoagulant therapy. Patients usually undergo rehabilitation therapy 3 times daily at rehabilitation hospitals. Trained rehabilitation staff performed pulse checks for each patient before, during, and after rehabilitation (9 times daily). If an irregular pulse and tachycardia (heart rate of 120 beats/min or faster) were detected, a 12-lead ECG immediately (within 5 min) after pulse assessment was essential to confirm or rule out AF (Figure 1). For patients with identified AF, the prescription will be changed to an anticoagulant at the rehabilitation hospital and the study office will be contacted. If the attending physician at the rehabilitation hospital has concerns about the prescription, the study office will consult about the prescription. The duration of the regular pulse monitoring is all periods from obtaining consent to admission in rehabilitation hospital.

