**Patient characteristics**
Age, sex, height, weight, modified Rankin Scale (mRS) score, type of stroke, hypertension, dyslipidemia, diabetes mellitus, chronic kidney disease, congestive heart failure, cerebrovascular disease, peripheral artery disease, peripheral artery disease, thromboembolism, active cancer, dementia, alcohol intake, smoking, antithrombotic therapy, functional independence measure (FIM), and mini mental state examination stroke (MMSE)

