**Events in the hospital**
Infection (urinary tract infection, pneumonia, cholecystitis, and other), recurrent stroke, falls

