### Data analysis plan

2.7.

We will examine the proportion of patients with AF detected, timing of detection, and characteristics of patients with AF. Clinical characteristics such as sex, age, laboratory data, echocardiography data, and brain imaging data, and outcomes will be compared between the patients in the AF and non-AF group. Sub-group analyses will be planned for patients who used other long-term electrocardiographic monitors, such as ICM. All statistical analyses will be performed using the SPSS software (version 27; SPSS Japan, Inc., Tokyo, Japan). The results will be considered statistically significant at *p* < 0.05. Univariate analyses will be performed using *χ*^2^ and Mann–Whitney *U* tests, as appropriate. Data will be presented as medians and interquartile ranges. Categorical variables will be presented as frequencies and percentages.

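### The outcome comparison between AF and non-AF patients uses unadjusted tests on groups formed during the stay, so it should be adjusted, split at detection and labelled descriptive

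*Protocol article*

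**What the plan says.** The evidence comes from five places in the protocol article.

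- **Entry (2.3 Patient population).** Exclusion criterion "2) patients with AF or atrial flutter" means that no one belongs to the AF group at enrolment.
- **Detection and treatment (2.4 Evaluations and follow-up).** Pulse checks run over the monitoring period at the rehabilitation hospital, with no fixed length. On detection treatment changes: "For patients with identified AF, the prescription will be changed to an anticoagulant at the rehabilitation hospital".
- **Outcomes (Table 2).** In-hospital events are infection, "recurrent stroke, falls". mRS, MMSE and FIM are recorded at discharge. The baseline list also contains mRS, "functional independence measure (FIM), and mini mental state examination stroke (MMSE").
- **Analysis (2.7 Data analysis plan).** The first aim is "We will examine the proportion of patients with AF detected, timing of detection, and characteristics of patients with AF". Characteristics "and outcomes will be compared between the patients in the AF and non-AF group". On method: "Univariate analyses will be performed using" chi-square and Mann-Whitney U tests. On the threshold: "The results will be considered statistically significant at" p<0.05. No adjustment, and no separation of events before and after detection, is named.
- **Introduction.** AF becomes more common with age, and once AF is present anticoagulants prevent recurrence better than antiplatelet drugs.

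**The concern.** The groups are not fixed at the start of follow-up. A patient enters the AF group when AF is found, and that can happen at any point in the stay. Three consequences follow.

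1. **Timing.** A recurrent stroke, infection or fall before detection counts in the AF group in the same way as one after it. The two mean different things, because treatment has changed in between.
2. **Opportunity.** A longer stay gives more pulse checks and more time for events. Length of stay alone can therefore link AF to events.
3. **Baseline differences.** The article itself ties AF to age. If AF patients are older or more disabled on arrival, an unadjusted test of discharge mRS, FIM or MMSE carries that difference forward, although the baseline values are at hand.

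A significant difference could then be read as prognosis, or as an effect of finding and treating AF, when it may be neither.

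**Working it through.** The plan has no figure to reproduce here. The sample size of 1000 is a count of expected admissions, and no detection rate, event rate or length of stay is given. Every rate below is an assumption, used only to show what the stated comparison does when there is no true association.

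**Inputs (assumed).** Detection hazard a = 0.0005 per day. Recurrence hazard r = 0.0003, 0.0005 or 0.001 per day. Equal thirds with stays L of 30, 60 and 90 days. Detection and recurrence are independent given L.

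**Case 1: monitoring continues after a recurrence.**
- P(AF | L) = 1 − exp(−aL) = 0.01489, 0.02955, 0.04400. The sum is 0.08844 and the mean 0.0295, or about 29 AF cases in 1000 patients.
- For r = 0.0005 the event probabilities are the same three numbers.
- Risk in AF group = (0.01489² + 0.02955² + 0.04400²) / 0.08844 = 0.00303 / 0.08844 = 0.0343.
- Risk in non-AF group = (0.08844 − 0.00303) / (3 − 0.08844) = 0.0293.
- Risk ratio = 1.17. For r = 0.0003 and 0.001 it is also 1.17 (0.0207/0.0177 and 0.0673/0.0577).
- With a single fixed stay, P(AF) cancels and the ratio is exactly 1.00. The excess comes wholly from varying length of stay: mean stay is about 70 days in detected patients and 60 in the others.

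**Case 2: a recurrence ends monitoring.**
- P(AF | L) = [a/(a+r)] × [1 − exp(−(a+r)L)]. For r = 0.0005 this is 0.01478, 0.02912, 0.04303, with sum 0.0869.
- P(AF and event | L) = [1 − exp(−rL)] − [r/(a+r)] × [1 − exp(−(a+r)L)]. The three values sum to 0.00152.
- Risk in AF group = 0.00152 / 0.0869 = 0.0174. Risk in non-AF group = (0.08844 − 0.00152) / (3 − 0.0869) = 0.0298.
- Risk ratio = 0.58. For r = 0.0003 and 0.001 it is 0.58 and 0.59.

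**Events available.** In case 1, the expected recurrences after detection in 1000 patients are about 0.3, 0.5 and 1.0 at the three recurrence hazards. They are about half of all AF-group recurrences (0.6, 1.0 and 2.0).

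**Different assumptions.** I also simulated 1000 patients with skewed stays (median 75 days), detection of 2%, 5% or 10% and recurrence of 5% per 80 days. The crude risk ratio was 1.22 to 1.29 if all events counted, and 0.58 to 0.63 if a recurrence ended the stay.

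**Discharge scores.** In the same simulation AF had no effect on the score. The Mann-Whitney test at 0.05 rejected as follows.

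| Confounding present | Rejection rate |
|---|---|
| None | 4% to 6% |
| Age only | 10% to 30% |
| Severity, through length of stay, only | 14% to 48% |
| Both | 31% to 91% |

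The ranges run over the three detection rates. Assumed effects: age on detection, log-hazard 0.5 per SD; age on score, 0.3 SD; severity on score, 0.5 SD.

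**The case against.** **No causal aim is stated.** The article evaluates feasibility, AF detection and anticoagulant initiation, then timing and patient characteristics. It nowhere says that the outcome comparison estimates the prognosis of AF or the benefit of finding it. This stands, and it limits the weight of the point.

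**The article is condensed, and a fuller plan may add adjustment.** It may. But section 2.7 names the comparison, the tests and the threshold, so the point concerns a stated method and not an omission. Naming univariate tests does not exclude further models.

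**A reader might infer that the plan builds in immortal-time bias and will make AF look protective.** The documents do not support that. Nothing says that a recurrence ends the stay or the monitoring, and the ratio near 0.6 needs exactly that rule.

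**A reader might blame the 1.17 on counting pre-detection events in the AF group.** That is also wrong. With a fixed stay those events are still counted and the ratio is 1.00.

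**A time-varying Cox model looks like the natural cure.** With about 29 AF cases and one post-detection recurrence or fewer, it could hardly be estimated. Adjusting for length of stay is debatable too, since stay is itself observed after enrolment and may respond to AF or to complications.

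**Baseline imbalance will be visible**, because age and other characteristics are compared between the same groups. True, but showing an imbalance does not remove it from the discharge comparison.

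**Conclusion.** The point holds for the outcome comparison only. Groups formed during a stay of no fixed length, a treatment change tied to membership and unadjusted tests together give a result that cannot be read as an effect of AF or of its detection.

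Its size cannot be fixed from the article. The null risk ratios of about 1.17 and about 0.6 show that the direction turns on whether monitoring continues after an event. They rest on assumed hazards, assumed stays and independence. The false-positive rates for discharge scores rest on assumed age and severity effects. I take monitoring to cover the rehabilitation stay; section 2.4 words its end point unclearly.

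A reader might infer that the study's main results are compromised. They are not: the proportion with AF detected and the proportion starting anticoagulants do not depend on this comparison. Describing baseline characteristics by later AF status is also ordinary and unobjectionable.

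**What to change.** In section 2.7:

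1. **Discharge scales.** Compare FIM and MMSE by regression and mRS by ordinal regression, each adjusted for the baseline value of the same scale and for age. Keep covariates few, because AF cases may be few.
2. **Recurrent stroke, infection and falls.** Report events before and after AF detection separately, as counts and rates per patient-day with confidence intervals. Use time-varying AF status in a model only if there are enough post-detection events.
3. **Wording.** Call the outcome comparison descriptive, and say that AF status and the accompanying treatment change cannot be separated.

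The baseline scales are already collected and detection timing is already to be examined. The added cost is recording the date of each event, some modelling, and wide intervals that should be shown as such. Nothing in patient care changes.

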### Study organization

2.8.

The ESCORT study was organized by a central coordinating center in the Department of Neurology, Nippon Medical School, and is being conducted at six medical partner institutions in Tokyo, Japan.

## Results

3.

Study recruitment began in September 2022 and will end in August 2023. The patients provided written informed consent and are currently in the enrollment phase. Data clean-up and analyses are projected to be completed by August 2023, and the results are expected to be submitted for peer-reviewed publications.

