**Results:**

The study is in the enrollment phase. Recruitment began in September 2022 and will end in August 2023. Patients have provided written informed consent. The main results have been submitted for publication in your journal.

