**Status at discharge**
mRS at discharge, MMSE at discharge, FIM at discharge, and discharge destination (home, hospital, convalescent home, other)

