### Sample size

2.6.

Notably, this study has not been previously reported. The number of possible participants in the study in a year was calculated from the number of admissions at participating facilities in the previous year and set at 1000.

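### Recruitment and analysis are both dated to finish in August 2023, which leaves no time to observe the last enrolled patients to discharge

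*Protocol article*

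**What the plan says.** On recruitment, section 3 (Results) of the protocol article states "Study recruitment began in September 2022 and will end in August 2023", and the Abstract gives the same end month. On analysis, section 3 states "Data clean-up and analyses are projected to be completed by August 2023" and expects the results to be submitted afterwards. The Abstract, having said that the study is still enrolling, states "The main results have been submitted for publication in your journal".

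The data to be analysed build up over the hospital stay. Table 2 lists in-hospital events (infection, recurrent stroke, falls) and, for status at discharge, "mRS at discharge, MMSE at discharge, FIM at discharge, and discharge destination". Section 2.4 describes pulse checks around every rehabilitation session and names the proportion with AF detected among the evaluated parameters. Section 2.7 adds the timing of detection and a comparison of characteristics and outcomes between AF and non-AF groups, using chi-square and Mann–Whitney tests.

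The planned number in section 2.6 "was calculated from the number of admissions at participating facilities in the previous year and set at 1000". The article gives no length of stay, no later data cut-off, and no rule for patients still in hospital when the data are closed.

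**The concern.** A patient enrolled in the last weeks of August 2023 cannot complete a rehabilitation stay, have discharge scores recorded, have the data cleaned and be included in a finished analysis within the same month. At least one of the stated dates must give way, or late enrollees must be analysed on incomplete data.

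The second outcome would matter for the study's main quantities. The proportion with AF detected and the timing of detection both depend on how long each patient is observed. Late enrollees would contribute less observation time and no discharge mRS, MMSE or FIM. The tests named in section 2.7 compare two groups as if every patient had been observed for a comparable period. The loss would not be random either: among patients enrolled on the same day, those still in hospital at a calendar cut are by construction the ones with longer stays.

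**Working it through.** **Inputs from the article.** Recruitment runs from September 2022 to August 2023, taken as 1 September to 31 August, or 365 days (section 3). Analysis is complete by August 2023 (section 3). The planned number is 1000 (section 2.6). The 1000 cannot be reproduced, because the site admission counts behind it are not given. It serves here only to turn percentages into counts.

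**Assumptions.** Accrual is uniform, the full 1000 are enrolled, and the length of stay L is varied because the article states none.

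**Step 1, the gap.** End of analysis minus end of recruitment: August 2023 − August 2023 = 0 months. About 1000/12 = 83 patients would enrol in the final month alone.

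**Step 2, patients still in hospital at the end of August 2023.** With uniform accrual over 12 months and a mean stay of L months, the expected share is L/12.

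**Step 3, monitoring time lost.** With equal stays, patients still in hospital have on average completed half of theirs. The lost share of planned monitoring time is therefore (L/12) × 1/2 = L/24.

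| Assumed stay (months) | Still in hospital, L/12 | Per 1000 enrolled | Monitoring time lost, L/24 |
|---|---|---|---|
| 1 | 8.3% | 83 | 4.2% |
| 2 | 16.7% | 167 | 8.3% |
| 3 | 25.0% | 250 | 12.5% |
| 5 | 41.7% | 417 | 20.8% |

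A day-by-day count over 365 days agrees: 82 patients at 30 days, 164 at 60, 247 at 90 and 411 at 150, with 4.2%, 8.4%, 12.5% and 20.7% of monitoring time lost.

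**Step 4, time for cleaning.** If 30 days before the end of August are kept for cleaning and analysis (assumed), the incomplete share becomes (L + 30)/365. This is 60/365 = 16.4% for a 30-day stay, 120/365 = 32.9% for 90 days and 180/365 = 49.3% for 150 days.

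**Step 5, effect on the detection proportion.** As an illustration, assume a true 5% detection over a 90-day stay at constant hazard. The hazard is −ln(0.95)/90 per day. Averaging 1 − exp(−hazard × days observed) over all enrolment dates gives about 4.4%, or 44 detected cases per 1000 instead of 50. The shortcut 5% × (1 − 0.125) = 4.4% gives the same answer.

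**The case against.** The strongest reply is that section 3 gives a projection in a status paragraph. It is neither a database lock nor a follow-up rule. Nothing in the article says that observation will be cut short, and the analysis date may simply be a mistake or out of date. That stands: truncation follows only if the timetable is kept. The printed dates still conflict with the outcomes to be collected and need correcting.

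The reply also limits several stronger readings that a reader might infer:

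- *That an unplanned interim analysis is being presented as final.* The only support is the Abstract sentence on submitted results. The Abstract also says that enrolment continues, and section 3 places submission in the future. The sentence reads like stray drafting and is weak evidence of an early analysis.
- *That patients still in hospital will be counted as non-AF.* Section 2.7 gives no rule for them, and such handling may sit in a full protocol or analysis plan that is not shown.
- *That those patients are the more disabled ones.* This is plausible for long stays, but the article does not say it, and being incomplete at the cut also depends heavily on enrolment date.
- *That 8% to 42% measures lost detection.* It counts patients with any part of the stay unobserved. The lost monitoring time is about half that.

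Two further limits apply. Discharge scores are survey items in Table 2 and are not among the three evaluated parameters in section 2.4. That section also describes the monitoring period as follows: "The duration of the regular pulse monitoring is all periods from obtaining consent to admission in rehabilitation hospital". This end point is hard to square with checks made at sessions during the stay, and the two statements must be reconciled. The loss of discharge outcomes does not depend on how that is settled; the loss of AF observation time does.

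**Conclusion.** The point holds as a conflict of dates with a consequence for the analysis, at moderate severity. The zero-month gap and the disagreement between the Abstract and section 3 are certain, since both are on the page. For any stay of realistic length, the last enrollees cannot be fully observed on the stated calendar.

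The size is conditional. Under uniform accrual and assumed mean stays of 1 to 5 months, about 8% to 42% of patients would be undischarged at the end of August 2023, with about 4% to 21% of monitoring time lost if stays are of similar length. The counts per 1000 hold only if enrolment reaches 1000. The documents do not establish that truncation will occur, that unfinished patients will be labelled non-AF, or that results were analysed early.

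**What to change.** Define the data cut-off by event: discharge, death or withdrawal of the last enrolled patient, plus a stated cleaning period. With an assumed 90-day stay and 30 days of cleaning, that is 120 days, or about 4 months after 31 August 2023.

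If a calendar cut-off is kept, state it, treat patients still in hospital as censored for AF detection on that date, and report how many have no discharge assessment.

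In either case, correct the analysis date in section 3, and delete the Abstract sentence on submitted results or reconcile it with section 3.

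The cost of the event-based cut-off is a report delayed by a few months, with no new patients or procedures. The censoring option avoids the delay but leaves discharge outcomes missing for late enrollees. Ending recruitment earlier is not recommended as a substitute, because it would cut into the one-year accrual on which the planned number rests.

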## Discussion

4.

AF after non-cardiac stroke is often asymptomatic and paroxysmal; thus, AF is unlikely to be detected by strategies based on symptom-driven monitoring. AF is typically detected in stroke patients after admission, but can be missed during the acute phase in stroke centers. Long-term ECG monitoring improves AF detection rates (8–12); however, using this method as an insertable cardiac monitor is invasive and expensive. In Japan, patients are transferred to rehabilitation hospitals after acute treatment, which makes continuous ECG monitoring difficult. The Japanese Arrhythmia Guidelines recommends pulse check, a simple and inexpensive method, as a Class 1 method for AF screening. Early detection of atrial fibrillation is important to prevent recurrence; however, not all cases are detected immediately after a stroke. Thus, a method that enables continuous arrhythmia assessment after the acute phase in rehabilitation hospitals is required. Pulse monitoring is a simple and inexpensive method. If this project confirms the feasibility and usefulness of pulse checks for detecting AF and starting anticoagulant therapy in rehabilitation hospitals, it will be especially useful for the prevention of cardioembolic stroke, heart failure, and mortality.

## Conclusion

5.

This ESCORT study aimed to increase the awareness of AF detection among therapists and its utility in rehabilitation hospitals. Additionally, we hope that the findings of this study will facilitate the identification of previously undetected cases of AF among stroke patients in rehabilitation hospitals, leading to improved prevention of recurrent strokes.

## Data availability statement

The raw data supporting the conclusions of this article will be made available by the authors, without undue reservation.

